## Abstract

**Background:**

Prevalence of post-traumatic stress disorder (PTSD) is high in Pakistan both due to natural disasters and ongoing conflicts. Offspring of trauma survivors are at increased risk for mental and physical illnesses. Parental PTSD has been linked to troubled parent–child relationships, behaviour problems, trauma symptoms, and depression in children. This study aims to explore the acceptability, feasibility and indications of the effectiveness of group learning through play plus trauma-focused cognitive behaviour therapy (LTP Plus TF-CBT) for parents experiencing PTSD.

**Methods/Design:**

This is a two-arm pilot cluster randomised controlled trial (RCT). We aim to recruit 300 parents with a diagnosis of PTSD. The screening will be done using the Impact of Event Scale-Revised. Diagnosis of PTSD will be confirmed using the Clinician-Administered PTSD Scale-5 (CAPS-5). Union Councils from Peshawar and Karachi will be randomised into either group LTP Plus TF CBT arm or treatment as usual (TAU). The intervention includes 12 sessions of LTP Plus TF-CBT delivered weekly in the first 2 months and then fortnightly in a group setting by trained psychologists. The groups will be co-facilitated by the community health workers (CHWs). Parents will be assessed at baseline and 4th month (end of the intervention), using the Patient Health Questionnaire (PHQ-9), Generalised Anxiety Disorder (GAD-7) Scale, Client Service Receipt Inventory (CSRI), and Ages and Stages Questionnaire (ASQ-3)

**Discussion:**

This trial would help build an understanding of the acceptability, feasibility and indications of the effectiveness of a low-cost parenting intervention.

## Background

The American Psychological Association has defined trauma as an ‘emotional response to a terrible event such as an accident, natural disaster or rape etc’ (APA, 2016). Exposure to trauma leads to post-traumatic stress disorder (PTSD) (Stein *et al*., 2016). Low and middle-income countries (LMICs) have higher trauma exposure, with high rates of PTSD in post-conflict areas (Atwoli *et al*., 2015). Post-trauma symptoms can particularly overburden parents and cause withdrawal and conflict among family members (Harrison *et al*., 2014). It has been reported that trauma may be transmitted to offspring via parenting practices burdened with severe parental emotional distress (Song *et al*., 2014). Hence, trauma and PTSD in parents leads to increased risk for mental and physical illnesses in children (Creech and Misca, 2017; Palosaari *et al*., 2013), behavioural issues along with trauma-related symptoms (Creech and Misca, 2017), disturbed parent–child relationships such as child abuse (Cross *et al*., 2018; Montgomery *et al*., 2019), and high incidence and intergenerational spread of family violence (Olema *et al*., 2014; Timshel *et al*., 2017).

The prevalence of PTSD in Pakistan both due to natural disasters and on-going conflict is high (Khan *et al*., 2015). In a survey study (*N* = 500) in Islamabad in Pakistan, it was found that 20.2% people reported that they experienced direct trauma during the last 12 months (Naeem *et al*., 2012). Additionally, nearly half of those (45.3%) who directly experienced trauma in addition to an indirect exposure scored positive for PTSD, compared with one-fifth (20.8%) of those who only experienced indirect trauma (Naeem *et al*., 2012). Pakistan has been in constant turmoil for decades; the threat level varies from city to city and locality to locality. The incident on the 16th December (2014) at the Army Public School (APS) in Peshawar, Khyber Pakhtunkhwa (KPK) province, which involved the shooting of young children, teachers and other staff in addition to an attack a year later at Bacha Khan University (in KPK) in January 2016, have had a major impact locally, nationally and internationally. A further terrorist attack on students at Peshawar University on 1st December 2017 again left the whole country in a state of shock and emotional turmoil. There is evidence that such events affect even those who hear about them but certain groups, such as the parents of school-going children are most affected (Khalily, 2011).

A healthy and positive development is consistent with positive,nurturing and secure parent-child attachment, family-community, and community-society relationships that reinforce self-worth, minimise frustration, and promote self-confidence (Winston and Chicot, 2016). Positive and nurturing parent-child relationships are largely dependent upon parents' ability to offer a secure and consistent environment for their children. It is reported that parental involvement, in the form of family routines, parental monitoring and supportiveness, is a protective factor for children facing conflict and disruption (Dubow *et al*., 2012).

The impact of early parenting interventions on parents and infants has been reviewed and meta-analysis reported that parenting interventions are effective in improving parenting responsiveness (*d* = 0.77) (Mihelic *et al*., 2017). An integrated intervention called learning through play plus cognitive behaviour therapy (LTP Plus TF-CBT) has found to be effective in low resource settings such as Pakistan (Rahman *et al*., 2009; Husain *et al*., 2017a, 2020). The LTP aims to stimulate early child development and its central feature is a pictorial calendar devised for parents, depicting eight successive stages of child development from birth to 3 years (Centre, 2002). Evidence also exist on parenting interventions delivered in the face of conflict and displacement in Syria (El-Khani *et al*., 2016).

Primary findings indicate that caregivers who have difficulties managing their own stress in addition to the stress caused by the child's behavioural and emotional changes require support maintaining positive parenting strategies. Trauma-focused cognitive behaviour therapies (TF-CBTs) are defined as interventions that include a systematic focus on processing trauma memories (Ennis *et al*., 2020) and can be a potential intervention for trauma survivor parents. Trauma-focused cognitive-behavioural therapy has proven very helpful and is often the treatments of choice for individuals with PTSD (Watkins *et al*., 2018). However, implementation of trauma-focused interventions is hindered in LMICs because of limited access to evidence-based psychological treatments and socio-political instability (Chen *et al*., 2017).

We propose to investigate the acceptability, feasibility and preliminary effectiveness of a manual assisted learning through play (LTP) plus culturally adapted TF-CBT among parents with young children experiencing PTSD. LTP Plus is proposed as a low-cost intervention to improve parents' mental and physical health and promote healthy child development. The activities in LTP are meant to enhance the social and emotional development of children. The activities are designed in a way which requires parents to be sensitive to the children's needs and actively engage with them, thus strengthening attachment (Husain *et al*., 2017b, 2020). In the proposed study LTP will be integrated with adapted trauma-focused CBT (Naeem *et al*., 2015; Latif *et al*., 2020) and will be delivered in a group format. TF CBT delivered in group settings uses cognitive restructuring techniques to facilitate each group member in processing their trauma experience. Each participant in a group has the opportunity to narrate his or her personal story as other group members listen. Hence, there is potential for all group members to participate in trauma processing through both recounting their own traumatic experience as well as vicarious experiences of others'. TF CBT group models encourage: strength of the personal narrative, power of group support, members ‘stand together’ and hear the experiences of others without judgment (Foy, Eriksson, and Trice, 2001).

## Research question

Whether the LTP Plus TF CBT is more feasible, acceptable and potentially effective as compared to the routine care for parents of young children in Pakistan?

### Hypothesis

The LTP Plus TF CBT will be more feasible, acceptable and potentially effective as compared to the routine care for parents of young children in Pakistan.

## Method

### Design

This is a two-arm pilot cluster RCT. Both qualitative and quantitative assessments will be administered to all eligible participants at baseline and after 4 months (end of the intervention).

### Randomisation

Randomisation will be computer-generated by an off-site statistician. The unit of a cluster will be Union Councils. A union council forms the second-tier of local government and fifth administrative division in Pakistan, The Union Councils will be randomly allocated to one of the two arms; arm-1 is the intervention group receiving LTP Plus and TF-CBT whereas Arm-2 is routine care.

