### Study site and population

Participants will be recruited from community settings (e.g. primary care) in Peshawar and Karachi with the assistance of community health workers (CHWs). Karachi is the capital of the province of Sindh, and the largest city in Pakistan, the world's third most populated city (Karachi Metropolitan Corporation). Karachi is a metropolitan city with diverse populations of political and economic migrants, refugees from different religious, linguistic, provincial and national origins who move to settle permanently. Peshawar is the capital of the province KPK, situated close to the border of Afghanistan. It has gone through major changes as a result of the Soviet-Afghan war and ongoing conflicts.

The parents with children aged between 3 and 6 years old will be screened with the Impact of Event Scale-Revised (IES-R) 22-item scale (Sundin and Horowitz, 2002). Those scoring 24 or above will be eligible for a full assessment of PTSD measured by Clinician-Administered PTSD Scale-5 (CAPS-5). The IES-R has been successfully used in Pakistan (Latif *et al*., 2020).

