### Sample size

To have an effect size of 0.45, assuming 5% significance level, 80% power and 10% drop out (Husain *et al*., 2017b) during the study, we need to recruit 300 parents. The objective for which the larger sample size is needed relates to the intra-cluster correlation coefficient (ICC), which measures the degree of similarity in outcome amongst parents in the same cluster; for this, the key is the number of clusters (Rutterford *et al*., 2015). Moreover, groups (and hence clusters) of size around 10 is the optimal size for interventions such as LTP Plus TF-CBT (Biggs *et al*., 2020). We propose a minimum of 15 clusters in each of the LTP + TF-CBT and routine care arms, in order to be able to obtain a relatively precise estimate of the ICC and to check whether it might be greater in the LTP + TF-CBT and routine care arms as the former may have additional variation due to the delivery of the group-based therapy. We, therefore, expect to recruit around 300 parents (approximately 10 each from 15 LTP + TF-CBT and 15 TAU clusters) which will enable the estimation of recruitment and retention rates with sufficiently good precision to inform a full effectiveness trial.

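### The primary test includes neither city nor Union Council, although the councils come from two cities that the protocol describes as markedly different

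*Protocol article*

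**What the plan says.** The Randomisation section of the protocol article states "Randomisation will be computer-generated by an off-site statistician" and then "The Union Councils will be randomly allocated to one of the two arms". The abstract names both cities in one sentence: "Union Councils from Peshawar and Karachi will be randomised into either group LTP Plus TF CBT arm or treatment as usual (TAU)". Neither place mentions stratification, blocking or matching by city, and neither rules it out.

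Under Study site and population, the article writes "Karachi is a metropolitan city with diverse populations of political and economic migrants" and, of Peshawar, "It has gone through major changes as a result of the Soviet-Afghan war and ongoing conflicts". The Background adds that the threat level differs between cities and places two of the attacks it recounts in Peshawar.

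The Sample size section plans "approximately 10 each from 15 LTP + TF-CBT and 15 TAU clusters", so 30 clusters in all.

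The Statistical analysis plan section fixes the primary analysis as a two-sided, two-sample comparison of PTSD rates at 4 months at the 5% level. No city term and no cluster term is given. Further multivariable analyses are planned, with covariates described only in general terms. The ICC is to be calculated for the benefit of future research.

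**The concern.** City is a known feature of the design and, on the article's own description, a plausible predictor of a PTSD outcome. A test that treats all parents as independent and ignores city has no allowance for the arms ending up with different shares of Peshawar and Karachi councils. With only 30 units to allocate, an appreciable difference in shares is not rare unless allocation is restricted by city. Any gap in PTSD rates between cities then feeds into the arm comparison, while the test's standard error does not reflect it.

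Two results are at stake: the p-value attached to the indication of effectiveness, and the ICC. The Sample size section gives precision of the ICC as a reason for the number of clusters, so its value should be interpretable when a full trial is planned.

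**Working it through.** **The plan's own figure.** The Sample size section states: "To have an effect size of 0.45, assuming 5% significance level, 80% power and 10% drop out", giving 300 parents. For two means with standardised difference 0.45, n per arm = 2 × (1.96 + 0.84)² / 0.45² ≈ 78, or 156 in total, and about 174 after 10% dropout. Reaching 300 needs a design effect of 300 × 0.9 / 156 = 1.73, that is an ICC of 0.73 / 9 ≈ 0.08 with clusters of 10. The article states no ICC, so 300 is not reproduced from its stated inputs. That is a separate matter and does not decide this point.

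**Inputs from the article.** 15 clusters per arm; about 10 parents per cluster; 10% dropout, so 9 analysed per cluster and 15 × 9 = 135 per arm; two-sided 5% test; two cities.

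**Assumed, because the article gives no values.** 15 councils per city (10:20 also tried); overall 4-month PTSD rate 60%; city gap d of 0 to 30 points; within-city ICC of 0 to 0.08.

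**Chance of city imbalance under unrestricted 15:15 allocation.** If K is the number of one city's councils in the intervention arm, P(K = k) = C(15,k) × C(15,15−k) / C(30,15).
- 9:6 or worse: 46.6%
- 10:5 or worse: 2 × (0.0581 + 0.0120 + 0.0013 + 0.0001) = 14.3%
- 11:4 or worse: 2.7%

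With 10 and 20 councils per city, the chance that the arms' city shares differ by at least one third is 5.0%.

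**Shift in the arm difference.** Shift = d × (difference in city share). At 10:5 the share difference is 10/15 − 5/15 = 1/3, so d = 10, 20 or 30 points gives 3.3, 6.7 or 10 points. At the commoner 9:6 split the share difference is 0.2, giving 2, 4 or 6 points.

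**Type I error of the planned test, averaged over all allocations.** Simulation under no treatment effect, 20,000 runs per setting, within-city ICC 0:

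| City gap (points) | Not stratified | Stratified (8:7 and 7:8) |
|---|---|---|
| 0 | 5.1% | 5.1% |
| 10 | 6.6% | 5.2% |
| 20 | 9.4% | 5.2% |
| 30 | 14.6% | 5.7% |

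A hand check for the unstratified 20-point case: the share difference has SD 0.186, so city adds variance 0.20² × 0.186² = 0.00138. The binomial part is 2 × (0.24 − 0.01) / 135 = 0.00341. The sum is 0.00479. The test assumes 2 × 0.24 / 135 = 0.00356. The ratio of SDs is 1.16, and 1.96 / 1.16 = 1.69, which has a two-sided tail of about 9.1%, close to the simulated 9.4%.

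**Which part of the test is at fault.** With within-city ICC 0.05 and a 20-point gap:

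| Analysis and allocation | Type I error |
|---|---|
| Planned test, not stratified | 13.8% |
| Planned test, stratified | 10.1% |
| City-adjusted, no cluster term, not stratified | 9.8% |
| Cluster-level t-test without city, not stratified | 5.0% |
| Cluster-level analysis with city, not stratified | 5.2% |

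Across all settings without stratification, the cluster-level t-test without city stayed between 4.8% and 5.5%. If allocation is stratified, however, leaving city out of that test makes it conservative: 2.3% at a 20-point gap and 1.1% at 30 points (ICC 0). Including city keeps it near 5% either way.

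**Effect on the ICC.** With cities of equal size, a gap d adds variance d²/4 between clusters, against a total of 0.6 × 0.4 = 0.24. For d = 10, 20 or 30 points this adds about 0.01, 0.04 or 0.09 to an ICC that is not conditional on city.

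**The case against.** A reader might infer that the councils are allocated without stratification. The article does not support this. It is silent, it condenses a fuller protocol, and a restriction factor is the sort of detail such an article leaves out. A reader might also infer that no analysis adjusts for city. That holds for the primary test, but the additional multivariable analyses have unlisted covariates that could include city.

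A third tempting reading is that chance city imbalance biases the trial. It does not: over repeated randomisations it averages to zero, and a valid cluster-level analysis already allows for it, even without city. The excess false positives come from a test that ignores clustering, and city is one part of that clustering.

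The sizes also rest on values that the article does not give. In addition, every participant must meet CAPS-5 criteria at entry, so a difference in conflict exposure need not become a difference in 4-month PTSD rates. And this is a pilot seeking indications of effectiveness, so the efficiency gained by stratifying matters less than in a definitive trial.

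All of these objections stand as limits on the claim. None removes the central fact: the primary test is a stated choice, it omits both city and council, and a two-sided 5% significance level is attached to it.

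**Conclusion.** The point holds in limited form. The primary test is specified without city or Union Council, in a cluster trial across two cities that the article itself contrasts, and whether allocation is stratified by city is not stated.

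If allocation is unrestricted, with 15 councils per city, the planned test's error rate rises from about 5% to between 6.6% and 14.6% for city gaps of 10 to 30 points, before any within-city clustering is counted. If allocation is stratified, the city part almost disappears (5.2% to 5.7%). Within-city clustering still matters in that case: about 10% at an assumed ICC of 0.05. These sizes depend on the assumed councils per city, city gap, ICC and 60% overall rate.

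The remedy is therefore a model that handles clustering and includes city. That improves on the stated test whether or not allocation was stratified.

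**What to change.** 1. Replace the primary two-sample test with a cluster-level analysis or a mixed model with Union Council as the cluster and city as a fixed effect. Do the same for the secondary outcomes. City costs one degree of freedom. The cluster term is the larger change and is needed regardless of city.
2. Report the ICC conditional on city alongside the unconditional one, so that planners of a stratified or an unstratified full trial each have the figure they need. This needs no further data.
3. State in the Randomisation section whether allocation is stratified by city and how many councils each city contributes. If councils are not yet allocated and stratification is not already in place, randomise 1:1 within city, which is a small change to the allocation program. If they are already allocated, report the city split by arm and rely on the adjusted model.

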### Blinding

The proposed study will be a single-blind study. The outcome assessors will be blind to the allocation status.

### Study site and population

Participants will be recruited from community settings (e.g. primary care) in Peshawar and Karachi with the assistance of community health workers (CHWs). Karachi is the capital of the province of Sindh, and the largest city in Pakistan, the world's third most populated city (Karachi Metropolitan Corporation). Karachi is a metropolitan city with diverse populations of political and economic migrants, refugees from different religious, linguistic, provincial and national origins who move to settle permanently. Peshawar is the capital of the province KPK, situated close to the border of Afghanistan. It has gone through major changes as a result of the Soviet-Afghan war and ongoing conflicts.

The parents with children aged between 3 and 6 years old will be screened with the Impact of Event Scale-Revised (IES-R) 22-item scale (Sundin and Horowitz, 2002). Those scoring 24 or above will be eligible for a full assessment of PTSD measured by Clinician-Administered PTSD Scale-5 (CAPS-5). The IES-R has been successfully used in Pakistan (Latif *et al*., 2020).

#### Inclusion criteria

Parents over the age of 16 yearsLiving with their children age 3–6 yearsWho meet the criteria for CAPS-5Able to give informed consent

#### Exclusion criteria

Parents with diagnosed severe physical or learning disability or severe mental illness which prevents them from attending the LTP Plus group intervention. This will be assessed by the research team at the screening stage. Any disabilities will be identified by a relevant clinician (e.g. Psychiatrist).Those who expressed active suicidal ideation during screening.Current use of anti-depressant medication reported by the parents.

### Procedure

Trained CHWs will approach potential participants in community settings (e.g. primary care, basic health units) in both intervention and control clusters. CHWs will assess potential participants against eligibility criteria (accept the diagnosis of PTSD using CASP). All potentially eligible participants will be invited for a meeting with a trained researcher who will then administer CASP on otherwise eligible participants. After screening, a detailed Participant Information Leaflet (PIL) will be provided to eligible parents and written (thumb impression for participants who are unable to read and write) consent will be obtained. Trained researchers will complete baseline assessment with all consented participants. Participants in the intervention cluster will receive 12 group sessions of LTP Plus TF CBT over the period of 4 months. A follow-up assessment will be done with all the participants 4 months after baseline.

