### Intervention

#### Learning through play + trauma-focused cognitive behaviour therapy (LTP + TFCBT)

The culturally adapted parent-focused group intervention (LTP plus TF-CBT) will be delivered to parents by masters-level trained psychologists supported by CHWs weekly during the first 2 months and then fortnightly at schools either at school drop-off or pick-up time depending on participant's preference and other community settings. The parenting component of the intervention (LTP) will be led by the CHWs and psychologists will lead the TF CBT component of the intervention. We have published a large cluster RCT of integrated parenting intervention called LTP Plus CBT for depressed mothers where CHWs successfully delivered intervention facilitated by the psychologists (Husain *et al*., 2021). The Intervention will be delivered in 12 sessions of 60–90 min in addition to routine care. The LTP plus TF-CBT has two components;
Culturally adapted learning through play (LTP)Culturally adapted trauma-focused cognitive behaviour therapy (TF-CBT)

LTP aims to enable parents to improve their child's psychical and psychosocial development by educating about child development and the importance of parent-child play. The pictorial calendar, which starts from birth and exhibits eight stages of healthy child development until 6 years of age, is an important feature of LTP. To enable a better understanding of how learning and attachment works, the calendar comes with culturally adapted illustrations of parent-child play (Husain *et al*., 2020).

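### As written, community health workers approach and pre-screen parents in clusters already called intervention or control, so who is approached and who consents can depend on the arm

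*Protocol article*

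**What the plan says.** All references are to the protocol article.

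- **Randomisation:** "The Union Councils will be randomly allocated to one of the two arms". An off-site statistician generates the list. The section does not say when a council's allocation is released, or to whom.
- **Procedure, first contact:** "Trained CHWs will approach potential participants in community settings (e.g. primary care, basic health units) in both intervention and control clusters".
- **Procedure, first check:** "CHWs will assess potential participants against eligibility criteria". The bracket that follows makes sense only if the PTSD diagnosis is carved out of this check.
- **Procedure, diagnosis:** "All potentially eligible participants will be invited for a meeting with a trained researcher who will then administer CASP on otherwise eligible participants".
- **Procedure, consent:** "After screening, a detailed Participant Information Leaflet (PIL) will be provided to eligible parents". Written consent and the baseline assessment follow.
- **Intervention:** "The parenting component of the intervention (LTP) will be led by the CHWs and psychologists will lead the TF CBT component of the intervention".
- **Blinding:** "The outcome assessors will be blind to the allocation status". Nobody else is mentioned.
- **Exclusion criteria:** the disability and severe-illness exclusion is assessed by the research team at screening, with disabilities identified by a clinician.
- **Sample size:** about 10 parents from each of 15 clusters per arm. Estimating recruitment and retention rates for a full trial is a stated purpose.

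**The concern.** Randomising Union Councils balances councils. It balances the parents inside them only if entry into the study does not depend on the council's arm. Here the people who decide whom to approach belong to the cadre that runs part of the intervention, and the text describes them working in clusters that already carry an arm label. A CHW who expects to lead a 12-session group has reason to think first of parents likely to attend. A CHW in a routine-care council has no such reason. Parents may also weigh consent differently if they know whether a group is on offer.

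Two outputs are at stake. The first is the comparison of PTSD rates at 4 months: if the arms contain different kinds of parent, the difference mixes treatment with selection. The second is the recruitment rate, which would describe two different recruitment processes and be a poor guide for the full trial. That second output means the pilot status of the study does not remove the concern.

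**Working it through.** The point concerns the order of steps and has no figure of its own to reproduce. It was checked by setting the sections side by side.

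**1. Who acts at each step, and what limits discretion**

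| Step | Who | Limit stated in the article |
|---|---|---|
| Choosing whom to approach | CHWs | None |
| Pre-check of eligibility | CHWs | Mostly factual criteria (age, child's age, reported antidepressant use) |
| Symptom screen | Not specified | Fixed IES-R cut-off of 24 |
| Disability or severe-illness exclusion | Research team, clinician | Not left to CHWs under Exclusion criteria |
| PTSD diagnosis | Trained researcher | CAPS-5 interview |
| Consent | Parent, after screening | One leaflet mentioned, no arm-specific versions |
| Outcome assessment | Assessors | Blind to allocation |

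The two steps without an effective limit are the approach and the consent. Only about 10 parents are needed per council, and each CHW covers about 150 households, so the choice of whom to approach leaves real room.

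**2. What the analysis can undo.** Every entrant must meet CAPS-5 criteria, so the arms cannot differ in diagnosis at entry. They can differ in severity, motivation and ability to attend. The primary test is an unadjusted two-sample comparison of proportions. Baseline measures enter only in additional multivariable work, which can address measured imbalance but not unmeasured motivation.

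**3. Sensitivity to an assumed shift.** The article gives nothing from which to derive a shift, and the calculation uses a continuous outcome although the primary test is of proportions. It shows sensitivity only.

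- Analysed per arm: 300 × 0.9 / 2 = 135, or 135 / 15 = 9 per cluster.
- Design effect DE = 1 + (9 − 1) × ICC. SE in SD units = √(2 × DE / 135).
- No true effect; selection shifts the follow-up means by b SD. Two-sided rejection rate = 1 − Φ(1.96 − b/SE) + Φ(−1.96 − b/SE).
- Example: ICC 0.05 gives DE = 1.40 and SE = 0.144. With b = 0.2, b/SE = 1.39 and the rate is 28%.

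| Assumed ICC | b = 0 | b = 0.1 | b = 0.2 | b = 0.3 |
|---|---|---|---|---|
| 0 | 5% | 13% | 38% | 69% |
| 0.05 | 5% | 11% | 28% | 55% |
| 0.08 | 5% | 10% | 25% | 49% |

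The article states no ICC. The top value is the one at which its sample size is recovered: 78 per arm for an effect of 0.45 gives 156; 156 × (1 + 9 × 0.08) = 268.3, rounded up to 269; and 269 / 0.9 ≈ 299.

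**4. Timing.** Procedure counts 4 months from baseline, the Statistical analysis plan section counts 4 months from randomisation, and Design equates 4 months with the end of the intervention. Assume 8 weekly and then 4 fortnightly sessions. Session 12 then falls 7 + 4 × 2 = 15 weeks after session 1. Four months is 4 × 52 / 12 = 17.3 weeks, which leaves about 17.3 − 15 = 2.3 weeks between a parent's baseline and session 1. A longer wait puts that parent's follow-up before the last session. This holds under the present text too, because a group of about 10 must be filled first.

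**The case against.** The strongest reply is that the sequence is inferred. Randomisation gives no date of release, and naming both kinds of cluster in Procedure may only describe where recruitment happens. Counting follow-up from randomisation in one section and from baseline in another suggests the two were thought of as close together. This is also a journal article, and details of concealment may sit in a full protocol that is not shown. This stands in part: the article does not state outright that allocation comes first. But the point rests on what Procedure says. Anyone following that text would recruit in labelled clusters, and nothing in the article points the other way.

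Several stronger readings are tempting and are not supported:

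- **CHWs control eligibility.** They do not. A researcher makes the diagnosis and the research team assesses the illness exclusion. Procedure and Exclusion criteria differ on who checks what and should be aligned.
- **CHWs can move parents into the intervention arm.** Clusters are administrative areas. Only selective approach within a council is possible.
- **The same individuals recruit and deliver.** The article names the same cadre. Overlap is likely given local catchments, but it is not stated.
- **Parents know their arm when they consent.** This is possible but not stated.

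It is also fair that the study seeks only indications of effectiveness and plans a baseline comparison by arm. That comparison would reveal measured imbalance but not repair selection.

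**Conclusion.** The concern holds as a risk created by the text as written. CHWs approach and pre-screen in clusters already called intervention or control, the cadre also delivers part of the intervention, and blinding is claimed only for outcome assessors. The remaining discretion lies in who is approached and who consents.

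The size is unknown. A reader might infer a definite bias in favour of the intervention, for example by multiplying an assumed baseline shift of 0.2 SD by an assumed correlation of 0.5 to get 0.10 SD, or 0.10 / 0.45 = 22% of the planned effect. Neither input is in the article. Nor is the direction fixed, since a more severe intervention arm would bias against the intervention. The table above carries the same caution.

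The conclusion assumes that Procedure describes the true order of events and that no concealment from recruiters is specified elsewhere. On that footing this is an inexpensive improvement to make before recruitment starts, because selection at entry cannot be reliably corrected afterwards.

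**What to change.** 1. State in Randomisation and Procedure that the off-site statistician releases a Union Council's allocation only after that council's approximately 10 parents have been identified, screened, consented and assessed at baseline.
2. Where this is not feasible, keep those who approach and consent parents unaware of allocation, and use the same script and leaflet in both arms.
3. Report the numbers approached, eligible and consenting by arm and cluster, so that differential recruitment is visible.
4. Align Procedure with Exclusion criteria on who assesses which criterion.
5. Reconcile the three descriptions of the 4-month assessment (from baseline, from randomisation, at the end of the intervention), so that follow-up does not precede the last session.

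**Cost.** This is a re-ordering of steps with no extra visits. The statistician is already in place, and groups must be filled before session 1 anyway. The downside is that venue booking, and any training given only in intervention councils, come after recruitment in each council and can lengthen the gap from baseline to session 1. Training CHWs beforehand where possible, and completing each council's baselines in a short window, keeps that gap small.
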